#### Secondary outcome measures

Secondary outcomes include: (1) systemic inflammatory markers (IL-6, TNF-α); (2) neurological deficit severity assessed by the National Institutes of Health Stroke Scale (NIHSS); and (3) activities of daily living measured by the modified Barthel Index (MBI). All secondary outcomes will be assessed at T0, T1, and T2. The MBI serves both as an operational basis for rehabilitation intensity adjustment and as a secondary outcome measure. To avoid a feedback loop, the adjusted MBI (accounting for rehabilitation dose) will be used as the primary interpretative measure for this secondary outcome, while the raw MBI will be used only for rehabilitation adjustment and will not serve as a direct basis for outcome interpretation. The NIHSS may have a floor effect in the enrolled population; its score changes will be used only as a safety or exploratory reference and will not serve as a primary efficacy measure.

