### Mechanistic exploration

To explore potential associations between taVNS-mediated improvement in cardiorespiratory fitness and changes in autonomic function, resting-state electrocardiograms (5 min recordings) will be obtained at T0, T1, and T2. Time-domain (SDNN) and frequency-domain (HF) indices of heart rate variability will be analyzed as exploratory outcomes. These indices will not be subjected to multiplicity correction and will be used solely for exploratory purposes, not for causal inference.

Inflammatory markers (IL-6, TNF-α) remain secondary outcome measures, but their mechanistic interpretation is limited to exploratory analysis. No mediation model is prespecified, and these results will not be used for causal inference.

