### Sample size calculation

The sample size for this study was estimated based on the group-by-time interaction effect for the primary outcome, VO_2_peak. Given the current lack of direct prior data on the effect of taVNS on VO_2_peak in stroke patients, we referred to the standardized effect size (*d* = 0.58) reported in a randomized controlled trial in healthy populations (25). Considering the greater heterogeneity in stroke patients, a conservative moderate effect size assumption was adopted for sample size planning. The sample size calculation was based on the group-by-time interaction from repeated-measures ANOVA, while the primary analysis will use a linear mixed-effects model; the two approaches are consistent in their handling of repeated-measures data, and LMM is more robust to missing data, so the sample size adequacy is unaffected. *A priori* power analysis was performed using the *F* tests—ANOVA: Repeated measures, between–within interaction module in G * Power 3.1 software, with the following parameters: effect size *f* = 0.25, *α* = 0.05, power (1 − *β*) = 0.80, number of groups = 2, number of measurements = 3, correlation among repeated measures = 0.50, and non-sphericity correction *ε* = 0.75. The effect size conversion was based on the formula *f* = *d*/2 (for two-group comparisons), with *d* = 0.58 (healthy populations) converted to *f* = 0.25 (stroke patients). A conservative estimate was adopted considering the greater heterogeneity expected in stroke patients. The assumed correlation among repeated measures (*ρ* = 0.50) was based on the typical range (0.3–0.7) reported in similar stroke rehabilitation studies, taking the median value; the non-sphericity correction (*ε* = 0.75) was set as a conservative value recommended by the G * Power software manual. Under these assumptions, the required total sample size was estimated to be approximately 128 participants, i.e., approximately 64 per group. Accounting for a 20% dropout rate, a final sample size of 160 participants (80 per group) was planned. Given the current lack of direct data on the effect of taVNS on VO_2_peak in stroke patients, this study adopted a conservative estimate based on the effect size from healthy populations; future research may further define the clinically meaningful difference in this population.

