### Statistical methods

Statistical analyses will be performed using SPSS 26.0 and R 4.1.0, following the intention-to-treat principle. All tests will be two-sided, with a significance level of *α* = 0.05 unless otherwise specified for multiple comparisons. Statisticians will remain blinded to group allocation until data lock. All randomized participants will be retained in the intention-to-treat analysis. The per-protocol analysis will report the proportion and characteristics of participants who do not meet the effort criteria. Additional stratified analyses will be considered: (1) all randomized participants; (2) those meeting adequate-effort criteria; (3) those terminating due to cardiopulmonary limitation; and (4) those terminating due to neurological or motor limitation, to assess the robustness of the results. For the primary outcome, VO_2_peak will be analyzed using a linear mixed-effects model, with group, time, and their interaction as fixed effects and participant as a random effect (random intercept) to account for within-subject correlations; a random slope may be added if model fitting requires. Age, sex, baseline VO_2_peak, stroke type, disease duration, baseline National Institutes of Health Stroke Scale score, and recruitment source (hospital or community) will be included as prespecified covariates. In the model, the time factor (T0, T1, T2) is used to estimate longitudinal trends, while baseline VO_2_peak is included solely as a covariate to adjust for baseline differences; the two serve different functions and do not constitute redundant adjustment. The covariance structure will be selected from unstructured, compound symmetry, or first-order autoregressive models based on the Akaike information criterion or Bayesian information criterion. The primary treatment effect will be assessed based on the baseline-adjusted between-group difference in VO_2_peak at T1, and the effect estimate, 95% confidence interval, and corresponding *p*-value will be reported. For secondary outcomes, all four measures (interleukin-6, tumor necrosis factor-alpha, National Institutes of Health Stroke Scale, and modified Barthel Index) will be analyzed longitudinally using the same linear mixed-effects model as for the primary outcome. For variables with substantial deviation from normal distribution or violations of parametric assumptions, generalized linear mixed models or nonparametric methods will be used as supplements. To control for multiple comparisons, a Bonferroni correction will be applied for the four secondary outcomes, with the significance threshold set at *α* = 0.05/4 = 0.0125. The exploratory outcome (heart rate variability) will not be adjusted for multiple comparisons and will be used only for exploratory interpretation. For missing data, the primary analysis will use the linear mixed-effects model under the missing-at-random assumption, utilizing all available observed values. To assess robustness, multiple imputation by chained equations and per-protocol analysis will be conducted as sensitivity analyses. In addition, the originally prespecified repeated-measures analysis of variance will be performed as a complementary analysis for comparison with the primary results; if the sphericity assumption is violated, the Greenhouse-Geisser correction will be applied, and *post-hoc* comparisons will be performed using the Bonferroni method. The incidence of adverse events will be compared using Fisher's exact test. If the sample size permits, prespecified exploratory subgroup analyses will be conducted for stroke type (ischemic vs. hemorrhagic) and recruitment source (hospital vs. community), using interaction tests to assess potential effect modification, with results interpreted only as exploratory. Due to sample size constraints (80 participants per group), stratification was performed only for age and disease duration. Other heterogeneity factors, including stroke type, baseline NIHSS score, and baseline VO_2_peak, have been incorporated as prespecified covariates into the linear mixed-effects model for adjustment.

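### Bonferroni at 0.0125 for the four secondary outcomes is valid, but Holm's procedure gives the same 5% family-wise control and can only reject more; the gain is modest and conditional

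*Protocol article*

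**What the plan says.** In the protocol article, Statistical methods, the general rule is "All tests will be two-sided, with a significance level of *α* = 0.05 unless otherwise specified for multiple comparisons". For the secondary outcomes, "all four measures (interleukin-6, tumor necrosis factor-alpha, National Institutes of Health Stroke Scale, and modified Barthel Index) will be analyzed longitudinally" with the mixed model used for the primary outcome. The multiplicity rule follows: "a Bonferroni correction will be applied for the four secondary outcomes", "with the significance threshold set at *α* = 0.05/4 = 0.0125". The threshold is the same for every outcome, whatever the other three show. No step-down or other sequential procedure is described.

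Three other statements bear on the point:

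- Secondary outcome measures: "All secondary outcomes will be assessed at T0, T1, and T2". Each outcome therefore has two post-baseline visits, and Statistical methods does not name one contrast per secondary outcome.
- The same section says that the NIHSS may show a floor effect and that "its score changes will be used only as a safety or exploratory reference and will not serve as a primary efficacy measure". Mechanistic exploration says that the inflammatory markers "remain secondary outcome measures, but their mechanistic interpretation is limited to exploratory analysis".
- Sample size calculation: "a final sample size of 160 participants (80 per group) was planned". The calculation rests on the primary outcome alone. No effect size or power target is given for any secondary outcome.

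**The concern.** Single-step Bonferroni holds all four tests to 0.0125 even after some of them have been won. Strong control of the family-wise error does not require this. Once one null hypothesis has been rejected, at most three can still be true, and a threshold of 0.05/3 is enough for the next. Holm's procedure uses this and Bonferroni does not.

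At stake is the second, third or fourth secondary result. Suppose one outcome has passed and the next smallest p-value lies between 0.0125 and 0.0167. The plan would report that second outcome as non-significant, although 5% family-wise control permits rejection. The protocol's Introduction hypothesizes that inflammatory markers and neurological function improve together, and that is the setting in which a step-down rule helps. The primary analysis is not affected.

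**Working it through.** **1. The plan's own figure.** 0.05/4 = 0.0125, which reproduces exactly. Four tests at 0.0125 sum to 0.05. If they are independent, the family-wise error is 1 − (1 − 0.0125)^4 = 0.0491. The rule controls 5% when there is one test per outcome.

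**2. Holm on the same four p-values.** Order them from smallest to largest and compare with 0.05/4 = 0.0125, 0.05/3 = 0.0167, 0.05/2 = 0.025 and 0.05/1 = 0.05, stopping at the first failure. Any p-value at or below 0.0125 passes every step up to its own rank, so each Bonferroni rejection is also a Holm rejection. The first threshold is the same, so the probability of at least one rejection is identical.

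**3. Inputs for the size of the gain.**

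- n = 64 per group, the evaluable number in Sample size calculation (128 in total).
- d = 0.5: the protocol's f = 0.25 for the primary outcome with its formula f = d/2, borrowed here as an assumption.
- Correlation 0.3 between the four tests, an assumption, with 0 and 0.5 as the range.

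**4. Power of one test.** The expected z statistic is d × √(n/2) = 0.5 × √32 = 2.828.

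- At 0.05: Φ(2.828 − 1.960) = 80.7%.
- At 0.025: Φ(2.828 − 2.241) = 72.1%.
- At 0.0167: Φ(2.828 − 2.394) = 66.8%.
- At 0.0125: Φ(2.828 − 2.498) = 63.0%.

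The distance from 63.0% to 80.7% is the most that any step-down rule could recover for one outcome. Holm recovers part of it, depending on how many other outcomes pass first.

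**5. Simulation of four correlated two-sided z-tests** (power per truly affected outcome):

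| Outcomes truly affected | Bonferroni | Holm, correlation 0.3 | Holm, correlation 0 to 0.5 |
|---|---|---|---|
| 1 | 63% | 63% | 63% |
| 2 | 63% | 65% | 65–66% |
| 3 | 63% | 68% | 68–69% |
| 4 | 63% | 73% | 72–74% |

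No Bonferroni rejection was lost under Holm in any run. At correlation 0.3, the error with no true effect was 4.7% for both methods. With one true effect, Holm's error was about 4.5% at most for n = 64. The largest value over all scenarios was 5.0%, for both methods alike, with no true effect and independent tests. The probability of at least one significant secondary outcome was the same under both methods throughout, for example 98.1% for each with four true effects and independent tests.

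**6. Sensitivity.** With all four affected at d = 0.3 and 64 per group, power per outcome goes from 21% to 24–26%. With d = 0.5 and all 80 per group evaluable, it goes from about 75% to 75% (one affected), 77% (two), 79–80% (three) and 83–85% (four).

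**7. Dependence on the family.** The thresholds in step 2 are for four p-values. If T1 and T2 were both tested for each outcome at 0.0125, the bound would be 8 × 0.0125 = 0.10, or 1 − (1 − 0.0125)^8 = 0.096 if independent. A four-value Holm procedure would not repair that; all eight p-values would have to enter it.

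**The case against.** The strongest reply is that nothing here is wrong. Bonferroni is valid, prespecified, simple and correctly computed, and the protocol promises no secondary power. This stands in full, and the point is one of efficiency only.

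The second reply is that Bonferroni buys something: one fixed threshold per outcome and matching 98.75% confidence intervals. A reader might infer that secondary power is given away for nothing. The documents do not support that wording, because there is a trade. It is a small one here, since Statistical methods commits to a 95% interval for the primary effect and promises no simultaneous intervals for the secondary outcomes.

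The third reply is that the gain is small in the plausible cases. This also stands. Holm adds almost nothing if one outcome is affected and 2 to 3 points if two are. The gain of about 10 points needs a true effect on all four, including the NIHSS, for which the protocol raises a floor effect and which it treats as a safety or exploratory reference. No stated objective requires all four to be won.

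The fourth reply is that Holm is not a remedy for every possible family. A reader might take the four thresholds to hold whichever visits are tested. They do not; they presuppose one test per outcome.

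What remains is that Holm never does worse on rejections at the same family-wise error, needs no dependence assumption, and can be adopted in one sentence before enrollment begins.

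**Conclusion.** The point holds as an optional, cheap improvement and not as an error. The Bonferroni rule controls the family-wise error as stated, but Holm would control it equally and could confirm further secondary effects once one has passed 0.0125. Under d = 0.5, 64 per group and correlation 0.3, the gain per truly affected outcome is about 0, 2, 5 and 10 percentage points with one, two, three and four true effects. The effect size is borrowed from the primary outcome and the correlation is assumed, because the protocol gives neither for the secondary outcomes. That Holm rejects at least as much as Bonferroni does not depend on these assumptions; only the size of the gain does.

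A reader might infer that the current rule endangers the trial's secondary conclusions or lowers the chance of finding any secondary effect. The first is not supported, because the rule is valid and conservative. The second is false, because the first Holm step uses the same 0.0125.

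**What to change.** Replace the Bonferroni sentence in Statistical methods by: *The four secondary outcomes (one prespecified contrast per outcome) will be tested with the Holm step-down procedure at a family-wise two-sided alpha of 0.05, and Holm-adjusted p-values will be reported.* State the contrast and visit for each outcome. If more than one visit per outcome is to be tested, put all those p-values into the Holm family.

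The cost is one sentence. The protocol's Ethics and dissemination section says that the statistical changes so far preceded enrollment and that no trial data had been examined, so this one could be made on the same footing if it is made before enrollment starts. The small downside is that Holm has no equally simple simultaneous confidence intervals. Report unadjusted 95% intervals, labelled as such, or 98.75% intervals. With 98.75% intervals, say that an outcome may be significant under Holm although its interval includes no effect.

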
### Ethics and dissemination

This study has been approved by the Ethics Review Committee of Shaanxi Rehabilitation Hospital (initial protocol Version 1.0, Approval No.: 2025079, date of approval: August 7, 2025). A protocol amendment (Version 2.0) changing the sample size from 92 to 160 participants has been filed with the Ethics Committee, with the approval number and date unchanged (2025079, August 7, 2025). The trial registration information is as follows: registration number (ChiCTR2500114436), registration date (December 11, 2025), protocol version (Version 2.0), primary outcome (VO_2_peak normalized to body weight, mL/kg/min), primary time point (T1, end of week 4), and final sample size (160 participants, 80 per group). The planned recruitment period is from July 2026 to June 2027. The trial can be accessed using the registration number on the ChiCTR website (https://www.chictr.org.cn). The changes to the sample size and statistical analysis were made before the start of participant enrollment, and no trial data have been examined.

Before enrollment, all participants will receive face-to-face counseling to fully understand the study purpose, procedures, potential risks, and their rights, after which they will voluntarily sign written informed consent forms. Participants may withdraw from the study unconditionally at any time, with the reasons for withdrawal recorded, and their medical rights will not be affected. The results of this study will be submitted for publication in a peer-reviewed journal.

**SPIRIT guidelines:** This protocol has been prepared in accordance with the SPIRIT (Standard Protocol Items: Recommendations for Interventional Trials) guidelines. The completed SPIRIT checklist has been submitted as a Supplementary File.

## Discussion

We hypothesize that taVNS may improve cardiorespiratory fitness in stroke patients through the following potential pathways. Stroke often leads to sympathetic-parasympathetic imbalance, manifested as increased resting heart rate and reduced heart rate variability (27, 28). TaVNS may theoretically enhance vagal efferent activity, thereby contributing to the restoration of autonomic balance, optimizing cardiac chronotropic function, and improving cardiac function (29). The vagal anti-inflammatory pathway is considered a crucial bridge between the nervous and cardiovascular systems (30, 31), and taVNS may inhibit the release of peripheral inflammatory markers through activation of this pathway, thereby improving energy metabolism in skeletal and cardiac muscle (32, 33). In addition, the nucleus tractus solitarius has extensive fiber connections with the medulla, midbrain, and cortical motor areas; repeated taVNS stimulation may indirectly promote motor function recovery through neuroplasticity mechanisms.

Previous studies in healthy populations have suggested that taVNS may increase VO_2_peak and reduce inflammatory responses (25). This protocol attempts to extend these findings to the domain of cardiorespiratory rehabilitation in patients with subacute stroke. It should be noted that VO_2_peak is a surrogate/functional endpoint, not a direct measure of clinical cardiovascular outcomes such as myocardial infarction or cardiovascular death. VO_2_peak only reflects the highest value achieved by the patient during that specific test and does not represent a true physiological cardiopulmonary limit.

Currently, standardized stimulation parameters for taVNS in stroke rehabilitation are lacking. The parameter settings in this study (frequency 25 Hz, pulse width 200 µs, intensity set at or slightly above the sensory threshold) are based on parameter combinations previously validated as effective in earlier research (25), with adaptive adjustments considering the skin sensitivity of stroke patients and the anatomical characteristics of the auricular concha. These parameters were selected to balance neuromodulatory efficacy and patient tolerability.

Reduced cardiorespiratory fitness represents a significant obstacle to functional recovery after stroke and serves as an independent predictor of adverse cardiovascular prognosis (6). Conventional rehabilitation training has limited efficacy in improving cardiorespiratory fitness. If this study suggests the efficacy of taVNS, it may provide a clinically applicable adjunctive treatment that is early-interventional, easy to administer, and associated with high compliance, which theoretically could shorten the rehabilitation course.

### Limitations

This study has several limitations. First, the single-center design and relatively limited sample size may affect the generalizability of the findings. Second, although rigorous blinding procedures have been implemented (participants, clinicians, outcome assessors, and statisticians will remain blinded), the intervention implementers cannot be blinded due to the visibility of the stimulation device, which may introduce potential performance bias. Third, the stimulation parameters have not been fully optimized, and a single parameter combination may not adequately address the heterogeneity of responses across all patients. Fourth, the follow-up period is relatively short (4 weeks post-intervention), precluding assessment of long-term efficacy and preventive effects on hard cardiovascular endpoints after stroke (e.g., cardiovascular death, myocardial infarction, heart failure hospitalization). Fifth, although this study employs a sham stimulation control and incorporates blinding assessment, it remains impossible to completely rule out the possibility that participants may guess their group allocation based on perceived differences in sensation. To monitor blinding effectiveness, participants will be asked about their group guess (active stimulation, sham stimulation, or uncertain) at the end of each week during the treatment period. The proportion of correct guesses will be calculated and analyzed using a binomial test to determine whether it is significantly higher than 50%. If the correct guess rate at any assessment point is significantly higher than 50%, this will be reported as a limitation. It should be noted that this assessment is intended only to monitor blinding effectiveness and cannot substitute for a credible sham stimulation design. Sixth, respiratory rate and tidal volume were not controlled during HRV acquisition, which may affect the accuracy of high-frequency HRV measurements. Both HRV and inflammatory markers are exploratory analytical measures; their results are intended only to explore potential associations and cannot be used for causal inference. In addition, improvement in VO_2_peak is influenced by multiple factors and should not be directly attributed to improvements in autonomic or cardiac mechanisms. Seventh, the study population consists of patients with mild-to-moderate subacute stroke who are able to complete cardiopulmonary exercise testing. Therefore, the results cannot be directly generalized to patients with severe hemiparesis, bedridden patients, patients with substantial cognitive impairment, or those unable to complete CPET. Eighth, this study did not include a specific assessment of lower-limb motor function, and the association between improvements in VO_2_peak and motor recovery remains unclear. Future studies may consider incorporating lower-limb motor function measures, such as the Fugl–Meyer lower extremity scale or the 10 m walk test.
